## 8. Trial Procedures

All participants underwent neuro-otological testing and Gd-enhanced inner ear MRI within 2 weeks following their first consultation at our institution. Participants were instructed to record the date, time, severity, and duration of vertigo attacks in a self-reporting diary. We asked all participants to decide by the next consultation date in 2 weeks whether to receive PPT in addition to medications. The allocation to the additional PPT intervention was made by self-determination, and participants were then assigned to either the Control group or the PPT group, prescribed an osmotic diuretic at daily doses of 63 mg, and then followed.

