### 4-2 Secondary Objectives

To assess the frequency of vertigo attacks per months using self-reporting diary.

To assess hearing function by PTA thresholds once a month.

To assess vestibular function by max-SPEV and VOR gain every 4 months.

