## **7. Eligibility Criteria**

### **7-1 Study population**

Participants were required to be diagnosed as unilateral definitive MD according to the criteria of the AAO-HNS, with repeat definitive vertigo attacks of more than one per month for the 2 months prior to entering the study despite diet and lifestyle modifications. An additional entry criterion was a functionality level of 3 to 4. Fifty participants will be enrolled into the study.

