## 13. Statistical Considerations

### 13-1 Primary Outcomes

The primary outcomes in this study are:

To assess the change of EH volume and the frequency of vertigo attacks per months.

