### Self-check diary

# Self-check diary Date

\_\_\_\_MM, YYYY

Name: \_\_\_\_\_ ID: \_\_\_\_\_ Start date :

DD \_\_\_\_\_MM \_\_\_\_\_YYYY \_\_\_\_\_

| 1                 | 2                 | 3                 | 4                 | 5                            | 6                 | 7                      |
|-------------------|-------------------|-------------------|-------------------|------------------------------|-------------------|------------------------|
| Level of vertigo: | Level of vertigo: | Level of vertigo: | Level of vertigo: | Level of vertigo:            | Level of vertigo: | Level of vertigo:      |
| Stress level:     | Stress level:     | Stress level:     | Stress level:     | Stress level:                | Stress level:     | Stress level:          |
| Stress level:     | Activity Level:   | Activity Level:   | Activity Level:   | Activity Level:              | Activity Level:   | Activity Level:        |
| 8                 | 9                 | 10                | 11                | 12                           | 13                | 14                     |
| Level of vertigo: | Level of vertigo: | Level of vertigo: | Level of vertigo: | Level of vertigo:            | Level of vertigo: | Level of vertigo:      |
| Stress level:     | Stress level:     | Stress level:     | Stress level:     | Stress level:                | Stress level:     | Stress level:          |
| Activity Level:   | Activity Level:   | Activity Level:   | Activity Level:   | Activity Level:              | Activity Level:   | Activity Level:        |
| 15                | 16                | 17                | 18                | 19                           | 20                | 21                     |
| Level of vertigo: | Level of vertigo: | Level of vertigo: | Level of vertigo: | Level of vertigo:            | Level of vertigo: | Level of vertigo:      |
| Stress level:     | Stress level:     | Stress level:     | Stress level:     | Stress level:                | Stress level:     | Stress level:          |
| Activity Level:   | Activity Level:   | Activity Level:   | Activity Level:   | Activity Level:              | Activity Level:   | Activity Level:        |
| 22                | 23                | 24                | 25                | 26                           | 27                | 28                     |

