| Level of vertigo: | Level of vertigo: | Level of vertigo: | Level of vertigo: | Level of vertigo:            | Level of vertigo: | Level of vertigo:      |
| Stress level:     | Stress level:     | Stress level:     | Stress level:     | Stress level:                | Stress level:     | Stress level:          |
| Activity Level:   | Activity Level:   | Activity Level:   | Activity Level:   | Activity Level:              | Activity Level:   | Activity Level:        |
| 29                | 30                | 31                | Score             | Level of vertigo :           | Stress level: :   | Stress level: :        |
| Level of vertigo: | Level of vertigo: | Level of vertigo: |                   | 0 : Vertigo-free             | 0 : free          | 0 : no reduction       |
| Stress level:     | Stress level:     | Stress level:     |                   | 1 : a mild attack            | 1 : mild          | 1 : minor reduction    |
| Activity Level:   | Activity Level:   | Activity Level:   |                   | 2: Moderately severe attacks | 2 : moderately    | 2 : moderate reduction |
|                   |                   |                   |                   | 3 : severe attacks           | 3 : severe        | 3 : stay at home       |

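### The appended diary has no printed field for the time, duration or number of attacks that section 8 relies on, so as printed it yields vertigo days per month, not attacks per month

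*Protocol*

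**What the plan says.** Protocol section 8 (Trial Procedures) describes a record kept attack by attack: "Participants were instructed to record the date, time, severity, and duration of vertigo attacks in a self-reporting diary".

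Section 4-2 makes the diary the data source for an objective: "To assess the frequency of vertigo attacks per months using self-reporting diary". Section 13-1 then lists "the frequency of vertigo attacks per months" as a primary outcome beside the change in endolymphatic hydrops volume. Sections 4-1 and 4-2 rank it as secondary, so its standing differs between sections, but it is a named outcome in both places.

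Entry under section 7-1 also depends on a count of attacks: "repeat definitive vertigo attacks of more than one per month for the 2 months prior to entering the study".

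The only diary in the document is the "Self-check diary" in Appendix 1. It is a calendar with one cell per day of the month. Each cell carries a "Level of vertigo" entry plus stress and activity entries, all scored 0 to 3 against a key at the foot of the form.

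**The concern.** Section 8 and the form describe two different instruments. Section 8 implies one record per attack, from which a monthly count follows directly. The form implies one score per day, from which only the number of days with vertigo follows. Several attacks on one day become a single entry.

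This is not a detail that can be left to the statistical analysis plan, because no analysis can recover time, duration or number if the form did not collect them. At stake is whether an outcome that section 13-1 calls primary is measured as worded, and whether attacks during follow-up can be compared with the kind of attack that qualified a patient for entry.

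**Working it through.** **Step 1: compare section 8 with the form.**

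| Item | Section 8 | Appendix 1, as printed |
|---|---|---|
| Date | yes | yes, by calendar day |
| Severity | yes, per attack | one 0 to 3 level per day |
| Time | yes | no field |
| Duration | yes | no field |
| Number of attacks | follows from per-attack records | no field, and not derivable on days with more than one attack |

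Two of the four items in section 8 have no place on the form, a third is recorded per day instead of per attack, and the count cannot be rebuilt for days with several attacks.

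**Step 2: what can be derived.** Vertigo days per month are the number of days scored 1 or more. They equal attacks per month when no day has more than one attack. Otherwise they are lower.

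**Step 3: how much lower.** The protocol states no figure to reproduce. Its only attack rate is the entry floor in section 7-1, more than one per month. The rates below are therefore assumptions. If L attacks fall independently and at random over a 30-day month:

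- Expected vertigo days = 30 × (1 − exp(−L/30))
- Undercount = 1 − vertigo days / L

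| L (assumed attacks per month) | Expected vertigo days | Undercount |
|---|---|---|
| 1 | 0.98 | 1.6% |
| 2 | 1.93 | 3.3% |
| 4 | 3.74 | 6.4% |
| 8 | 7.02 | 12.2% |

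**Step 4: clustering.** If each attack day has m attacks on average, the undercount is 1 − 1/m. The protocol gives no value for m and the form cannot supply one. The direction is certain, since clustering enlarges the gap, but no size can be claimed.

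**Step 5: effect on a relative reduction.** Under the random model, a true fall from 8 to 4 attacks (50%) reads as 7.02 to 3.74 days, and 1 − 3.74/7.02 = 47%. A true fall from 4 to 1 (75%) reads as 3.74 to 0.98 days, and 1 − 0.98/3.74 = 74%. Under clustering with a constant m, percentage reductions do not change at all.

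**The case against.** The strongest reply is that the form is adequate in practice. It is dated, every non-zero level is worded as an attack, and at rates near the entry floor vertigo days and attacks almost coincide. Relative reductions are barely distorted in the examples above, and both arms use the same form. All of this stands, and it limits the point to a mismatch of measurement.

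Two further cautions also stand. Section 8 does not cite Appendix 1, and the two diary names differ, so it is strongly implied but not stated that they are the same instrument. The form was read from a PDF, so blank space in which patients might write a time or duration cannot be excluded.

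A reader might infer more than the document supports, in four ways:

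- That attack frequency cannot be obtained at all. It can, whenever no day has more than one attack.
- That the undercount is large. That needs clustering values which the protocol does not give.
- That self-selected arms turn the shortfall into bias. The protocol gives no attack rates by arm, and a constant clustering proportion would leave ratios between arms unchanged.
- That the key mixes severity with number, because level 1 is singular while "2: Moderately severe attacks" is plural. That rests on loose wording in a key that came through extraction imperfectly.

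It can also be said that the outcome is worded as vertigo attacks, without the qualifier used at entry. That is fair: the protocol does not require follow-up attacks to meet the entry definition. What remains is that, without duration, the printed form offers no means of checking whether they do.

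None of these replies removes the contradiction between section 8 and the printed fields.

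**Conclusion.** The point holds as a contradiction between section 8 and Appendix 1 in how a named outcome is measured. As printed, the form gives vertigo days per month and a daily severity level. It does not give attack counts, times or durations.

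The numerical consequence is small at low rates if attacks fall at random: about 3% at 2 attacks per month, 6% at 4 and 12% at 8. It would be larger, by an unknown amount, if attacks cluster within days. These figures rest on assumed rates and a 30-day month. The conclusion as a whole rests on the Appendix 1 form being the diary that section 8 means, and on its having no further writing space in use. It deserves correction because the missing items cannot be restored at analysis, but it does not show that the outcome is unusable or biased between arms.

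**What to change.** Reconcile section 8 with Appendix 1. If the form is not yet in use, add to each daily cell the number of attacks and the start time and duration of each. Severity should be recorded per attack if section 8 is to be met in full. The cost is a revised one-page form and slightly more writing for patients.

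If the form is already in use, which the past tense of section 8 suggests is possible, do not change it partway, because earlier and later diaries would no longer be comparable. Instead, state in sections 4-2, 8 and 13-1 that the outcome is vertigo days per month, name the level at which a day counts, and remove from section 8 the items that the form does not collect. This is a substantive change to an outcome and needs advance approval from the ethical review committees under section 15. Its cost is a less direct measure of attack frequency.

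In either case, state that the Appendix 1 form is the diary referred to in sections 4-2 and 8.

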### 8-1 Recruitment

Potential participants will be approached by their treating clinician (who in the case of this study may also be the CI/PI, Co-Investigator or PI-delegated clinician) during routine standard of care outpatient appointments at KRH. Potential participants will be given a participant information sheet (PIS) and the opportunity to ask questions before deciding whether or not to take part.

### 8-2 Informed Consent Process

It is the responsibility of the CI/PI Investigator, or a PI-delegated clinician to obtain written informed consent from each participant prior to participation in the trial, following adequate explanation of the aims, methods, anticipated benefits and potential hazards of the trial. “Adequate time” must be given for consideration by the participant before taking part. Consent will be sought at least 24 hours after being given the study documentation. It must be recorded in the medical notes when the PIS have been given to the participant. A copy of the signed informed consent form will be given to the participant. The original signed form will be retained in the trial file at site and a copy placed in the medical notes. Participants are under no obligation to enter the trial and can withdraw at any time during the trial without providing a reason.

The PIS and consent form will be reviewed and updated if necessary throughout the trial (e.g. where new safety information becomes available) and participants will be re-consented as appropriate.

## 9. Assessments and Follow up

Follow-up assessments were scheduled at monthly intervals. We performed audiometry once a month, video head impulse testing (vHIT) was performed every 4 months, and caloric testing and MRI were performed every 8 months. These tests were performed on the same day if tests coincided.

| Assessment   | First consultation | 1m | 2m | 3m | 4m | 5m | 6m | 7m | 8m |
|--------------|--------------------|----|----|----|----|----|----|----|----|
| Audiometry   | ○                  | ○  | ○  | ○  | ○  | ○  | ○  | ○  | ○  |
| vHIT         | ○                  |    |    |    | ○  |    |    |    | ○  |
| Caloric test | ○                  |    |    |    |    |    |    |    | ○  |
| MRI          | ○                  |    |    |    |    |    |    |    | ○  |

## 10. Treatment for adverse events

### 10-1 Responding to participants when an adverse event occurs

When an adverse event takes place, the people conducting the research will take appropriate action immediately and, whenever necessary, quickly provide transport to a medical facility. A record of this will be taken without contradiction in a case report form. Whenever treatment for an adverse event becomes necessary, this will be conveyed to the participants.

## 10-2 Reporting of Serious Adverse Events

All serious adverse events that occur during the study period and all serious adverse events that occur after the termination (discontinuation) of the study and are suspected of having a connection to the study will be reported. When an adverse event is confirmed to have occurred, a report will immediately be provided to a supervisor and CI/PI.

## 11. Data Management and Quality Assurance

Utmost consideration will be given to protecting the participants' confidentiality when documenting raw data and handling consent forms pertaining to the study. The results of the study, when published, will not contain any information that could be used to identify the participants. It will be mentioned that the data on the participants obtained during the study shall not be used for any purpose other than the objectives of the study. The participants' privacy will be kept confidential and consideration will be given to ensure that absolutely no personal information be leaked. The research representative is responsible for managing the data. Anonymized data will be disclosed, but individual data will not be published.

A trial specific data management will be in place for the trial. This will contain details of the software to be used for the database, the process of database design, data entry, data quality checks, data queries, data security, database lock.

## 12. Cost Burden on Participants

The participants shall bear none of the costs required in this study and received no stipend. However, Tests or drugs required to treat the primary disease and complicating diseases shall not be borne by the present study.

## 13. Statistical Considerations

### 13-1 Primary Outcomes

The primary outcomes in this study are:

To assess the change of EH volume and the frequency of vertigo attacks per months.

### 13-2 Secondary Outcomes

The secondary outcomes in this study are:

Hearing function (PTA thresholds)

Vestibular function (max-SPEV and VOR gain).

### 13-3 Sample Size Calculation

The sample size has been selected by the chief investigator and is based on formal statistical calculation or consideration.

### 13-3 Statistical Analysis Plan (SAP)

Full details of all planned statistical analyses will be included in a written Statistical Analysis Plan which will be completed before the final study database is locked for analysis. The main focus of all analyses will be on the group difference for the outcome construct, and statistical significance tests will be used sparingly.

## 14. Record Keeping and Archiving

Essential documents relating to the conduct of the study are kept in the Department of Otolaryngology and Head and Neck Surgery, Kansai Rosai Hospital. The CI is responsible for their storage. The documents will be kept for a minimum of five years after the termination of the study period. Tables corresponding to the participants' identities will be kept separately and anonymized. Documents will be disposed of by shredder

following the end of the storage period.

## **15. Changes to the Implementation Plan etc.**

In the event that there are any changes to the implementation plan or the informed consent form, the advanced approval of the ethical review committees will be required.

## **16. Complying with the Declaration of Helsinki**

This study will be conducted in compliance with the Declaration of Helsinki.

## **17. Monitoring Requirement for the Trial**

A trial specific oversight and monitoring plan will be established for this study.

## **18. Research Funds and Conflicts of Interest**

The present study will be conducted using the medical research fund of the Hyogo Medical Association and by research funds to promote the hospital functions of Japan Organization of Occupational Health and Safety. The planning, implementation, and reporting of the present study will be free of any "potential conflicts of interest" that would affect the results of the study or the interpretation of the results, and the rights and interests of the participants will not be neglected in the implementation of the study.

## **19. Compensation for health problems and obtaining insurance**

### **19-1 Compensation for health problems**

No compensation will be offered for losses caused by any lawful act.

### **19-2 Obtaining liability insurance**

To prepare for any liability, the research staff will be insured against liability.

## **20. Publication Policy**

The anonymized data will be put through a statistical analysis and published sequentially. The analysis results will be disclosed in the form of papers, conference presentations, reports, and mass media publications.

### Self-check diary

# Self-check diary Date

\_\_\_\_MM, YYYY

Name: \_\_\_\_\_ ID: \_\_\_\_\_ Start date :

DD \_\_\_\_\_MM \_\_\_\_\_YYYY \_\_\_\_\_

| 1                 | 2                 | 3                 | 4                 | 5                            | 6                 | 7                      |
|-------------------|-------------------|-------------------|-------------------|------------------------------|-------------------|------------------------|
| Level of vertigo: | Level of vertigo: | Level of vertigo: | Level of vertigo: | Level of vertigo:            | Level of vertigo: | Level of vertigo:      |
| Stress level:     | Stress level:     | Stress level:     | Stress level:     | Stress level:                | Stress level:     | Stress level:          |
| Stress level:     | Activity Level:   | Activity Level:   | Activity Level:   | Activity Level:              | Activity Level:   | Activity Level:        |
| 8                 | 9                 | 10                | 11                | 12                           | 13                | 14                     |
| Level of vertigo: | Level of vertigo: | Level of vertigo: | Level of vertigo: | Level of vertigo:            | Level of vertigo: | Level of vertigo:      |
| Stress level:     | Stress level:     | Stress level:     | Stress level:     | Stress level:                | Stress level:     | Stress level:          |
| Activity Level:   | Activity Level:   | Activity Level:   | Activity Level:   | Activity Level:              | Activity Level:   | Activity Level:        |
| 15                | 16                | 17                | 18                | 19                           | 20                | 21                     |
| Level of vertigo: | Level of vertigo: | Level of vertigo: | Level of vertigo: | Level of vertigo:            | Level of vertigo: | Level of vertigo:      |
| Stress level:     | Stress level:     | Stress level:     | Stress level:     | Stress level:                | Stress level:     | Stress level:          |
| Activity Level:   | Activity Level:   | Activity Level:   | Activity Level:   | Activity Level:              | Activity Level:   | Activity Level:        |
| 22                | 23                | 24                | 25                | 26                           | 27                | 28                     |
| Level of vertigo: | Level of vertigo: | Level of vertigo: | Level of vertigo: | Level of vertigo:            | Level of vertigo: | Level of vertigo:      |
| Stress level:     | Stress level:     | Stress level:     | Stress level:     | Stress level:                | Stress level:     | Stress level:          |
| Activity Level:   | Activity Level:   | Activity Level:   | Activity Level:   | Activity Level:              | Activity Level:   | Activity Level:        |
| 29                | 30                | 31                | Score             | Level of vertigo :           | Stress level: :   | Stress level: :        |
| Level of vertigo: | Level of vertigo: | Level of vertigo: |                   | 0 : Vertigo-free             | 0 : free          | 0 : no reduction       |
| Stress level:     | Stress level:     | Stress level:     |                   | 1 : a mild attack            | 1 : mild          | 1 : minor reduction    |
| Activity Level:   | Activity Level:   | Activity Level:   |                   | 2: Moderately severe attacks | 2 : moderately    | 2 : moderate reduction |
|                   |                   |                   |                   | 3 : severe attacks           | 3 : severe        | 3 : stay at home       |
